## Abstract

**Introduction and aim:**

Diabetes is a global health emergency with increasing prevalence and diabetes-associated morbidity and mortality. One of the challenges in optimising diabetes care is translating research advances in this heterogeneous disease into clinical care. A potential solution is the introduction of precision medicine approaches into diabetes care.

We aim to develop a digital platform called ‘intelligent Diabetes’ (iDiabetes) to support a precision diabetes care model in Scotland and assess its impact on the primary composite outcome of all-cause mortality, hospitalisation rate, renal function decline and glycaemic control.

**Methods and analysis:**

The impact of iDiabetes will be evaluated through a cluster-randomised controlled study, recruiting up to 22 500 patients with diabetes. Primary care general practices (GPs) in the National Health Service (NHS) Scotland Tayside Health Board are the units (clusters) of randomisation. Each primary care GP will form one cluster (approximately 400 patients per cluster), with up to 60 clusters recruited. Randomisation will be to *iDiabetes (guideline support*), *iDiabetesPlus* or *usual diabetes care* (control arm). Patients of participating primary care GPs are automatically enrolled on the study when they attend for their annual diabetes screening or are newly diagnosed with diabetes. A composite hierarchical primary outcome, evaluated using Win-Ratio statistical methodology, will consist of (1) all-cause mortality, (2) all-cause hospitalisation rate, (3) proportion with >40% estimated glomerular filtration rate [eGFR] reduction from baseline or new development of end-stage renal disease, (4) proportion with absolute HbA1C reduction >0.5%. Outcomes will be evaluated after a 2-year median follow-up period. Comprehensive qualitative and health economic analyses will be conducted, assessing the cost-effectiveness, budget impact and user acceptability of the iDiabetes platform.

**Ethics and dissemination:**

This study was reviewed by the NHS Health Research Authority and approved by the East of Scotland Research Ethics Committee (reference: 23/ES/0008). Study findings will be disseminated via publications, presented at scientific conferences and shared with patients and the public on the study website and social media.

**Trial registration number:**

ISRCTN18000901.

STRENGTHS AND LIMITATIONS OF THIS STUDYiDiabetes is a novel precision medicine platform which is the first of its kind to evaluate a precision diabetes care model in a controlled trial.The study evaluates real-world application in an existing healthcare system, with the entire regional diabetes population eligible for enrolment—results are therefore likely to be generalisable and the approach could be scaled up to a national level.The study analysis uses a mixed-method approach allowing a comprehensive evaluation of all aspects of the precision medicine platform including impact on clinical outcomes, usability for both patients and clinicians, cost-effectiveness analysis, budget impact analysis and patient preferences.Study enrolment takes place when patients attend their routine clinical diabetes review—consequently, a subpopulation of patients with limited healthcare access may be excluded.The patient-facing platform is only available in an English version and can only be accessed digitally; therefore, patients with limited English or digital illiteracy may not benefit from the intervention to its full potential.

## Introduction

### Background

Diabetes is increasing in prevalence worldwide, giving rise to a spectrum of associated comorbidities including cardiovascular, renal and liver complications and posing a significant global health crisis. These complications, along with the burden of living with a chronic illness, contribute to impaired quality of life and disability and ultimately increased mortality in people living with diabetes.^1^ Public health strategies have been unsuccessful at controlling the epidemic, and current pharmacological therapy is often suboptimal—focused largely on glycaemic regulation, with prescribing practice sometimes influenced by non-medical factors such as drug cost. As a result, opportunities to target therapy choice to underlying biological mechanisms of diabetes and relevant comorbidities may be overlooked.^2^

Recognising the highly heterogeneous nature of diabetes, the concept of precision diabetes medicine has garnered attention in modern diabetes care. Research breakthroughs in diabetes in recent decades create the potential for a revolution in care, incorporating a more comprehensive analysis of multiple biological factors, including genomic variations and metabolic pathways, with environmental risk factors for individual patients.^2^ For example, recent research has shed light on the heterogeneity of type 2 diabetes (T2D), which has traditionally been viewed as a uniform pathology. This heterogeneity exists as a continuum and is associated with both phenotypic and genotypic variations, resulting in differential disease progression, end-organ complications and treatment response.^3 4^ Additionally, predictive algorithms derived from patient-level characteristics within a UK-based population database demonstrated that this phenotypic heterogeneity could be used to guide treatment choices (eg, for choosing between sodium-glucose transporter 2 [SGLT2] inhibitor vs dipeptidyl peptidase-4 [DPP4] inhibitor) to optimise glycaemic control.^5^ More recently, clinical diagnostic models incorporating clinical features and biomarkers (such as pancreatic autoantibodies and Type 1 Diabetes (T1D) Genetic Risk Score) may allow enhanced differentiation between T1D and T2D at the time of diagnosis.^6^ Similarly, the identification of monogenic forms of diabetes has allowed for the cessation of unnecessary diabetes treatment in patients with *GCK*-MODY and spared patients with other forms, such as neonatal diabetes and *HNF1A*-MODY, from unnecessary insulin injections.^7^,^9^ However, incorporating these advances into routine clinical care, translating them to direct benefit to patients, is challenging and can be slow. For example, despite being well described in the literature, it has been estimated that approximately 80% of monogenic diabetes cases remain undiagnosed, highlighting the need for more effective ways to translate research outcomes into routine clinical care.^10^

Introducing precision medicine in diabetes care, as outlined in the consensus American Diabetes Association/European Association for the Study of Diabetes Precision Diabetes Medicine Initiative report, requires the transformation of the current care approaches.^11^ Using a range of data, a more refined diabetes care model should be developed, which encompasses all aspects of the disease—disease prevention, timely diagnosis, personalised treatment, individualised prognosis and appropriate monitoring of diabetes.

### Implementing precision diabetes care in Scotland

We aim to develop and assess an innovative ‘intelligent Diabetes’ (iDiabetes) platform to support and implement a precision diabetes care model, delivered at scale, to patients with diabetes managed in both primary and secondary care in the Tayside Health Board region of Scotland. The platform aims to facilitate precision diagnosis and promotes the selection of optimal treatments by healthcare professionals while ensuring that these diagnoses and treatment recommendations are effectively communicated to patients.

This study will compare two different arms of the iDiabetes platform to usual diabetes care. The *iDiabetes (guideline support*) arm will use routinely collected clinical and biochemical data to produce individualised treatment recommendations.

The *iDiabetesPlus* arm will combine routinely collected clinical and biochemical data with additional biochemical and genotypic testing to determine a patient’s risk of current and future end-organ diabetes complications and predicted glycaemic response to different pharmacotherapies. This information will be used to generate enhanced individualised treatment recommendations.

The treatment recommendations generated in both arms of the iDiabetes platform will allow healthcare professionals to make better-informed, individualised evidence-based treatment decisions, thereby improving the management for each patient. If demonstrated to improve patient care and to be cost-effective, the vision is for iDiabetes to be the standard of care for patients with diabetes across Scotland.

### Study objectives

#### Primary objective

Develop a precision medicine platform for diabetes care and assess its impact on the primary composite outcome (mortality rate, hospitalisation rate, decline in renal function and glycaemic control) of patients with diabetes.

#### Secondary objectives

Assess the impact of a precision medicine platform on the individual components of the composite outcomes of patients with diabetes.Evaluate the impact of a precision medicine platform on hospitalisation rate secondary to heart failure.Evaluate patients’ adherence to antidiabetic medications, cholesterol-lowering medications and antihypertensives.Evaluate the impact of iDiabetes platform treatment recommendations on the rate of severe hypoglycaemia.Evaluate whether recommendations from iDiabetes platform improve healthcare professionals’ compliance with guideline recommendations during the prescription of antidiabetic medications.

Additional exploratory objectives will include further assessment of the impact of iDiabetes on end-organ diabetes-associated complications, qualitative and cost-effectiveness analysis of the platform. A full list of exploratory objectives can be viewed in the online supplemental file 1.

## Methods

### Study design

This is a three-arm cluster-randomised controlled study (two iDiabetes arms and usual diabetes care control arm), with a nested qualitative study and economic evaluation. The inclusion of two different arms within the iDiabetes platform allows evaluation of the clinical utility and cost-effectiveness of the addition of guideline-based recommendations (*iDiabetes (guideline support*)) to patients’ usual diabetes care as well as the additional value gained from precision diagnosis and treatment resulting from the addition of enhanced phenotyping and genotyping to guideline support (*iDiabetesPlus arm*).

### Randomisation

Each primary care general practice (GP) within the National Health Service (NHS) Tayside Scottish Health Board region will form one of up to 60 clusters. NHS Tayside provides primary healthcare to approximately 417 650 people in the northeast of Scotland, in both urban and rural communities within the region.^12^ Practices will be stratified by population size (<6000 or ≥6000 registered patients) and index of deprivation deciles (1–3 high deprivation, 4–7 medium and 8–10 low).^13^ Clusters will be randomised to one of the following three arms: *iDiabetes (guideline support*), *iDiabetesPlus* or *usual diabetes care* (see figure 1). All 60 clusters (approximately 400 patients per cluster) will undergo initial randomisation to the iDiabetes platform or *usual diabetes care* arms in a 2:1 ratio. Clusters initially allocated to the iDiabetes platform will undergo a second randomisation to *iDiabetes (guideline support*) or *iDiabetesPlus* in a 1:1 ratio, resulting in overall cluster allocation of 1:1:1 for *iDiabetes (guideline support*), *iDiabetesPlus* and *usual diabetes care* arms.

**Figure 1 F1:**
[figure not shown]
Cluster randomisation with each GP practice forming a cluster. Map at the top left corner of the figure shows the geographical area covered by the NHS Tayside Health Board in Scotland (generated via paintmaps.com). GP, general practice; NHS, National Health Service.

The randomisation will be created by the UK Clinical Research Collaboration-registered Tayside Clinical Trials Unit. The study participants, primary care GPs and study clinicians will not be blinded. Blinding would not be possible as test results will be accessible to healthcare professionals and patients as part of the iDiabetes platform design, and the tests undertaken will be determined by the study arm; therefore, this will make the study arm known. Additionally, specific consent is required for genetic testing, which is only performed in the *iDiabetesPlus* arm. There are no planned criteria for stopping or switching a patient’s enrolment in an iDiabetes intervention arm.

### Recruitment of primary care GPs

All primary care GPs in NHS Tayside will be invited to participate in the study. The study team will actively promote the study and engage with primary care GPs to encourage their participation. This will ensure that the adequate sample size is met at cluster level.

### Recruitment of participants and follow-up period

Patients will be enrolled in the study when they attend for their routine annual diabetes screening appointment or are newly diagnosed with diabetes in primary care during the study period. Recruitment will stop when 7500 patients, with diabetes of any type, have been enrolled in each arm. Recruitment into the *usual diabetes care* arm will be allowed to continue up to a maximum of 9000 patients if this arm reaches completion earlier than the *iDiabetes (guideline support*) or *iDiabetesPlus* arms. It is anticipated that the total recruitment period will be 12–15 months.

The planned study follow-up period will be until a median of 2 years of follow-up has been completed across all patients recruited into the study.

Study recruitment will begin in October 2024.

### Eligibility criteria

#### Inclusion criteria

Patient registered with an NHS Tayside Health Board primary care GP practice which has signed up and agreed to commit for the duration of the study.Diagnosis of any diabetes type.Aged ≥18 years at the time of diabetes annual review during the study period.

#### Exclusion criteria

There will be no exclusion criteria. All patients identified as meeting the inclusion criteria will be included in the study.

### Intervention

The iDiabetes platform will form the central intervention in this study. The iDiabetes platform will incorporate patient data and facilitate the generation of recommendations based on the most recent evidence for each patient. The recommendations will be accessible by both healthcare professionals, via the iDiabetes dashboard, and by patients themselves, via My Diabetes My Way (MDMW). MDMW is an interactive online patient portal used by patients with diabetes in Scotland. It provides them with information about their condition and secure access to their own diabetes-related healthcare records, including test results.^14^ For all patients enrolled in the study, there will be no restriction or implication for any other concomitant care or interventions provided by the patients’ usual care team as the iDiabetes platform is a tool to support decision-making only.

#### iDiabetes (guideline support)

Patients will attend their annual diabetes review and be assessed as per usual care including routine diabetes blood testing (see table 1). The iDiabetes platform will generate automated, individualised treatment recommendations using routine clinical data and blood test results from annual appointments. Recommendations will be determined by the latest treatment guidelines such as the *American Diabetes Associations’ Standard of Care for Diabetes* and the *National Institute for Health and Care Excellence Clinical Knowledge Summaries*.^15 16^ Recommendations on optimisation of medications for associated comorbidities will also be provided where a patient has renal or cardiovascular disease. For example, advice will be given to optimise ACE inhibitor or angiotensin receptor blocker for patients with proteinuria or optimise statins for patients with cardiovascular disease.

**Table 1 T1:** Blood tests, risk scoring systems and imaging tests performed by iDiabetes platform.

	Blood tests	Risk scoring	Imaging
Renal	▪ Creatinine▪ Laboratory-measured eGFR▪ Urinary albumin:creatinine ratio**▪ eGFR calculated by 2021 CKD-EPI Creatinine**	**▪ Kidney failure risk equation**	
Cardiology	▪ **NT-proBNP▪ hsTroponin I**	▪ **Coronary Artery Disease Polygenic Risk Score**	▪ **Echocardiography (either standard echocardiography or AI decision-supported [US2Ai] echocardiography)***
Liver	▪ ALT▪ Bilirubin▪ Alkaline phosphatase▪ **AST**▪ **Ferritin/ transferrin saturations**†▪ **Hepatitis B and C**†	▪ **FIB-4 score**†▪ **NAFLD Fibrosis Score (NFS)**†▪ **Enhanced Liver Fibrosis (ELF) Score**†	▪ **Liver Fibroscan**†
Diabetes aetiology	▪ HbA1C▪ **C-peptide and paired glucose**‡▪ **Pancreatic autoantibodies testing**‡	▪ **Type 1 Diabetes Polygenic Risk Score**‡▪ **MODY probability**‡	

Tests in bold will be performed in *iDiabetesPlus* arm only

* US2.AI-supported echocardiography will be performed in patients with NT-proBNP between 400 and 2000 pg/mL pg/mL. Standard echocardiography will be performed via the current urgent clinical pathway if NT-proBNP >2000 pg/mL.

† Non-invasive lliver ffibrosis sscoring, ferritin/ transferrin saturations and hepatitis B and C testing if ALT >30 IU/L. ELFELF testing will be triggered if FIB-4 >1.45 or NFS >−1.455. Fibroscan will be performed on patients with FIB-4 >3.25, NFS >0.677 or ELF ≥9.8.

‡ The cascade of biomarkers for confirmation of diabetes diagnosis will only be triggered in patients with a clinical diagnosis of type 1 diabetes and those at high risk of MODYMODY.

ALTAlanine aminotransferaseASTAspartate transferaseCKD-EPIChronic Kidney Disease Epidemiology CollaborationeGFRestimated Glomerular Filtration RateELFEnhanced Liver Fibrosis scoreFIB-4Fibrosis-4 indexMODYMonogenic diabetesNFSNAFLD Fibrosis ScoreNT-proBNPN-terminal pro-B-type natriuretic peptide

#### iDiabetesPlus

Patients will undergo routine assessments at their annual diabetes review in the same way as *iDiabetes (guideline support*). However, in addition to the routine diabetes blood testing, *iDiabetesPlus* will incorporate additional reflexive laboratory testing, including C-peptide concentration, cardiac risk biomarkers ± echocardiography, non-invasive liver fibrosis scoring ± Fibroscan and individual genotyping (to allow for cardiovascular and T1D genetic risk scoring) (see table 1). Enhanced phenotyping and genotyping will allow for improvement in diagnostic accuracy of diabetes type and determination of current and future risk of end-organ complications. Recommendations on optimisation of medications for associated comorbidities will be provided in the same way as *iDiabetes (guideline support*) with additional recommendations for patients with liver disease. Further to this, risks of myocardial infarction and all-cause mortality will be predicted for patients with T2D using models developed by MyWay Digital Health. Treatment recommendations for each patient will be evidence-based and determined according to their competing cardiorenal or liver risk, risk of hypoglycaemia and predicted diabetes drug treatment response using a treatment selection algorithm. All recommendations will be accessible to the patient and their diabetes care team (see figure 2).

**Figure 2 F2:**
[figure not shown]
An overview of iDiabetesPlus. ACEi, angiotensin-converting enzyme inhibitor; ARB, angiotensin receptor blocker; BP, blood pressure; GLP1RA, glucagon-like-peptide 1 receptor agonist; IHD, ischaemic heart disease; SGLT2i, sodium-glucose transporter 2 inhibitor; SLD, steatotic liver disease; 1 unit of alcohol = 8 g of ethanol.

#### Usual diabetes care

This will form a control arm. Patients will attend their usual annual diabetes appointment and be managed as per the usual care by their diabetes care provider, with no additional intervention from the iDiabetes platform or study team.

### Development of iDiabetes platform

The iDiabetes platform will be made possible through the development of a novel software called iDiabetes IQ engine which will be registered as a class 1 medical device under the current UK Medical Device Directive according to International Standards Organisation standards (see figure 3).^17^ Comprehensive information regarding data source and exchange for the software will be provided in a separate article on the programming of iDiabetes IQ engine. In this section, we provide a brief overview of the steps involved in developing the software.

**Figure 3 F3:**
[figure not shown]
An overview of the iDiabetes IQ engine. SCI, Scottish Care Information; MWDH, *MyWay Digital Health*; MDMW, *My Diabetes My Way*.

#### Development of algorithms

The iDiabetes IQ engine software will consist of a series of rules-based algorithms encompassing three main themes: diagnosis of diabetes, risk stratification of end-organ complications and diabetes treatment recommendations. The *iDiabetes (guideline support*) and *iDiabetesPlus* algorithms were developed from a collaboration among expert clinicians using the latest guidelines, evidence and expert opinion.

#### From algorithms to iDiabetes dashboard content

The algorithm pathways were first converted into ‘pseudocode’ (a readable but detailed description of what the software should do), and the ‘pseudocode’ was translated into digital code by the iDiabetes software developers. iDiabetes dashboard contents were created, which included explanatory text and links to external patient and clinician resources. A dashboard explanatory text was created for every recommendation generated by the algorithm. These will be viewable by healthcare professionals during clinic reviews. A lay version of the content was developed for patients to access via MDMW.

#### iDiabetes IQ engine performance testing

To ensure that the iDiabetes IQ engine is functional and reliable, user acceptance testing was conducted to test its performance. A large 'ground truth' dataset was created, with simulated patient data created to match every possible recommendation output. Ground truth patients were run through the algorithm to ensure all outputs matched the expected algorithm output. A subsequent full end-to-end testing, using an anonymised real-world dataset extracted from SCI-Diabetes, was performed. Any disparities between expected and observed outputs were fully scrutinised and where necessary the software code was updated. A pilot phase on the roll-out of the iDiabetes platform will facilitate a final period of real-world platform testing prior to the commencement of the full study.

#### Data input

Data input to the iDiabetes IQ engine will be sourced from SCI-Diabetes, an integrated clinical system with linked electronic health records from primary and secondary care, specialist screening services and laboratory systems for all patients with diabetes across NHS Scotland.^18^ All patients’ clinical data and blood test results, both historical and that obtained during recruitment (when attending annual diabetes clinic appointment) will be available within the SCI-Diabetes system.

### Study outcomes

#### Primary outcome

A composite hierarchical outcome (in decreasing order of clinical importance):

All-cause mortality.All-cause hospitalisation rate.Proportion with >40% eGFR reduction from baseline, or new development of end-stage renal disease (ESRD).Proportion with absolute HbA1C reduction >0.5% (>5.5 mmol/mol).

#### Secondary outcomes

All-cause mortality rate.All-cause hospitalisation rate.Proportion with >40% eGFR reduction from baseline, or new end stage kidney disease.Proportion with absolute HbA1C reduction >0.5% (>5.5 mmol/mol).Hospitalisation rate secondary to heart failure.Drug adherence (medication possession ratio).Rate of severe hypoglycaemia.Proportion of patients treated according to guidelines.

Outcomes which can be measured in the *usual diabetes care* arm as well as the iDiabetes intervention arms have been selected to allow comparison. Therefore, in decreasing order of importance, we rank (1) all-cause mortality, as failure to consider mortality can introduce issues of competing risk; (2) all-cause hospitalisations, as these are common and a major burden to patients and healthcare systems; (3) renal function decline, as this is a major morbidity in diabetes—a fall in eGFR of >40% is in keeping with clinical trials focusing on renal outcomes as the endpoint; (4) HbA1c reduction >0.5% (5.5mmol/mol), as HbA1c is a major driver of both microvascular and macrovascular disease in diabetes. HbA1c is not ranked higher despite its importance in diabetes as many treatment recommendations provided by iDiabetes (eg, for heart failure, coronary artery disease, renal disease and steatotic liver disease) are HbA1c independent, in which HbA1c lowering is not our primary goal. All items in the composite will also be analysed and reported individually as secondary outcomes. All outcomes will be measured at individual patient level.

Additional exploratory outcomes will include further assessment of the impact of iDiabetes on end-organ diabetes-associated morbidity and diabetes treatment and a full qualitative and cost-effectiveness analysis of the platform. A full list of exploratory outcomes can be viewed in the online supplemental file 1.

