#### Health economics analysis

A model-based cost-effectiveness analysis of the *iDiabetes (guideline support*) and *iDiabetesPlus* arms versus the *usual diabetes care* arm will be conducted. The cost per complication avoided and Quality-Adjusted Life Year gained (the standard health economic utility measure) for each strategy will be predicted by incorporating the study data into an existing diabetes simulation model.^23^,^25^ To estimate the resource implications of introducing the iDiabetes platform at scale in NHS Scotland, a budget impact analysis will be conducted. This will assess whether the recommendations from the cost-effectiveness analysis model are affordable to NHS Scotland.

The DCE data will be used to (1) assess the relative importance of attributes in the delivery of personalised diabetes care; (2) predict patient uptake of alternative treatment plans and (3) estimate benefit-risk trade-offs associated with the risk of adverse outcomes. The DCE data will complement the cost-effectiveness analysis evidence, ensuring that the iDiabetes platform is valued by service users.

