#### Echocardiography consent

For iDiabetesPlus patients with a pro-BNP 400 to 2000 pg/mL, further evaluation for heart failure will be performed using AI-assisted echocardiography using US2Ai echocardiography software. An additional PIS will be sent and informed consent obtained for patients prior to undergoing US2Ai echocardiography. For those who do not wish to consent they will be offered a routine NHS echocardiography appointment.

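### Heart-failure hospitalisation is compared between arms, but only iDiabetesPlus tests for heart failure, so both comparisons with Plus may reflect labelling as well as disease

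*Protocol article*

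**What the plan says.** The Secondary outcomes section of the protocol article lists "Hospitalisation rate secondary to heart failure", and the Secondary objectives name it as a target of the evaluation. The same outcomes section explains the choice of outcomes: those that can be measured in the usual care "arm as well as the iDiabetes intervention arms have been selected to allow comparison".

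Table 1 marks NT-proBNP, high-sensitivity troponin and echocardiography in bold, and its note reads "Tests in bold will be performed in" the iDiabetesPlus arm only. The table footnote gives the cascade: "US2.AI-supported echocardiography will be performed in patients with NT-proBNP between 400 and 2000 pg/mL", and "Standard echocardiography will be performed via the current urgent clinical pathway if NT-proBNP >2000 pg/mL". The Echocardiography consent section confirms that in Plus "further evaluation for heart failure will be performed using AI-assisted echocardiography using US2Ai echocardiography software". The Usual diabetes care section adds no study testing.

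The Randomisation section (text under Figure 1) says that participants, practices and study clinicians are not blinded, because "test results will be accessible to healthcare professionals and patients as part of the iDiabetes platform design". The section on quantitative data collection says that outcome data come through routine linkage. The Secondary statistical analysis section treats the listed secondary outcomes as exploratory and promises a full analysis plan before data-lock.

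**The concern.** An outcome can be measurable in every arm without being ascertained equally in every arm. All-cause death, all-cause hospitalisation, laboratory eGFR and HbA1c do not need anyone to decide why a patient was admitted. Heart-failure hospitalisation does. In Plus, a raised NT-proBNP or an abnormal echocardiogram may already be on record when a breathless patient is admitted. In the other two arms the study adds no such test. The same admission could then be labelled differently depending on allocation.

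Heart failure is among the conditions that the article names as targets of recommendations not driven by HbA1c, so this is an outcome where Plus might be expected to show a benefit. If labelling differs by arm, a null or adverse result could not be told apart from better detection, and a favourable one could be partly a labelling effect too. The difference comes from the intervention itself, so a larger sample does not remove it.

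**Working it through.** **The plan's own figures.** The article gives no heart-failure admission rate, effect size or power, so there is no stated figure to test. The nearest is 81% power for all-cause hospitalisation (45% versus 37%, 40 clusters, ICC 0.03). It reproduces. There are 60/3 = 20 clusters per arm and 7500/20 = 375 patients per cluster. The design effect is 1 + 374 × 0.03 = 12.22 and the effective size 7500/12.22 = 614 per arm. A two-sided two-proportion test at 5% then gives 81.4%. That figure is not in dispute and does not bear on labelling.

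**Effect of unequal labelling.** For each arm, let c be the number of admissions labelled heart failure divided by the number truly due to heart failure. Missed labels lower c and false labels raise it. Let k = c(Plus)/c(comparator). Then

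observed rate ratio = true rate ratio × k.

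All values of k below are assumptions.

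| True ratio | k = 1.05 | k = 1.10 | k = 1.25 | k = 1.40 | k that erases the benefit (1/true ratio) |
|---|---|---|---|---|---|
| 0.80 | 0.84 | 0.88 | 1.00 | 1.12 | 1.25 |
| 0.90 | 0.945 | 0.99 | 1.125 | 1.26 | 1.11 |

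If labelling ran the other way by the same proportion, k = 1/1.10 = 0.91, and a true 0.80 would appear as 0.80/1.10 = 0.73, an exaggerated benefit.

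**One plausible range.** Suppose 70–85% of true heart-failure admissions are labelled as such in usual care and 85–95% in Plus, with no false labels. Then k runs from 0.85/0.85 = 1.00 to 0.95/0.70 = 1.36, and a true 0.80 appears as 0.80 to 1.09. The midpoints give 0.90/0.775 = 1.16, so 0.80 appears as 0.93. These shares cannot produce k below 1, so they illustrate size and say nothing about direction.

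**How little relabelling is needed.** Let heart failure be a share f of control admissions (assumed 2–10%), with the same number of other admissions in both arms. The share of those other admissions that must be relabelled in Plus to erase a true ratio RR is f(1 − RR)/(1 − f).

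- RR 0.80: 0.02 × 0.20/0.98 = 0.4% up to 0.10 × 0.20/0.90 = 2.2%.
- RR 0.90: 0.02 × 0.10/0.98 = 0.2% up to 0.10 × 0.10/0.90 = 1.1%.

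**Which companion outcome resists relabelling.** Move one emergency breathless admission from a respiratory label to heart failure:

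| Outcome | Change in count |
|---|---|
| Heart-failure admission, including main diagnosis only | +1 |
| Any cardiovascular admission | +1 |
| Any cardiovascular or respiratory admission | 0 |
| All-cause hospitalisation | 0 |

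A cardiovascular-only companion therefore shifts with the outcome it is meant to check. All-cause hospitalisation does not shift, but it is insensitive: with f = 2–10% and no effect on other admissions, a true heart-failure ratio of 0.80 gives an all-cause ratio of 1 − 0.20f, that is 0.996 to 0.98. The cardiovascular-or-respiratory group dilutes less, provided heart failure is a larger share of it than of all admissions.

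**Scope.** None of the four components of the primary composite depends on a cause of admission, and creatinine, laboratory eGFR and HbA1c are not in bold, so they are measured in every arm. Guideline support and usual care both lack the bold tests, so that comparison is free of this mechanism. Plus versus usual care and Plus versus guideline support are the two exposed comparisons.

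**The case against.** The article claims only that its outcomes can be measured in all arms, and that is true of heart-failure hospitalisation. Diagnosis position, adjudication and sensitivity analyses are normally left to the analysis plan. The article does not say who assigns the cause of admission, or whether those people see the platform's results. The endpoint needs an admission, and a screen-detected diagnosis alone does not count. All-cause hospitalisation is already reported, and the outcome is exploratory.

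Most of this stands and limits the point. Missing coding detail is not the finding. What remains is that the design creates an asymmetry in what is known about heart failure, and the stated rationale for comparability does not deal with it.

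A further argument is that screening may truly reduce heart-failure admissions. That effect sits in the true rate ratio; labelling multiplies it and is a separate matter.

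A reader might infer that the bias must run against Plus and make it look harmful. The documents do not support that. A low NT-proBNP or a normal echocardiogram on record could remove heart-failure labels as well as add them, and reversal of a true 0.80 needs k above 1.25.

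A reader might also infer that the exploratory end-organ comparisons and the economic output ("The cost per complication avoided and Quality-Adjusted Life Year gained") are distorted in the same way. The list of exploratory outcomes is in a supplement that is not shown. The article says that costs per complication are predicted by feeding study data into an existing simulation model, without describing the inputs. That extension can only be conditional.

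**Conclusion.** The point holds for heart-failure hospitalisation in the two comparisons that involve iDiabetesPlus. Arm-specific testing, unblinded clinicians who can see the results, and outcomes from routine records are all stated. A difference in labelling is therefore credible, and it could mask, attenuate or exaggerate an effect. More labelling in Plus is the likelier direction, but neither direction nor size can be taken from the article. Under assumed factors of 1.05 to 1.40, a true ratio of 0.80 would appear as 0.84 to 1.12. Equal labelling would leave it at 0.80.

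The primary conclusion of the trial is not at risk. The consequence is limited to the interpretation of one exploratory secondary outcome, but one that speaks directly to a stated aim of the platform. It should be changed, and there is time to do so before the analysis plan is published.

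**What to change.** 1. Define heart-failure hospitalisation as emergency admission with heart failure as the main diagnosis. This is still a label, so it does not suffice alone.
2. Prespecify beside it emergency admission for any cardiovascular or respiratory cause, and report both with the all-cause hospitalisation already planned.
3. State that a heart-failure benefit or harm for Plus will be interpreted only in the light of these companions, and record the difference in ascertainment as a limitation.
4. If any exploratory end-organ comparison or model input counts newly recorded diagnoses, report those found through Plus-only tests separately from complications that surface clinically.

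The cost is wording in the analysis and health-economics plans and one extra coded outcome from data already linked. The companion is less specific and dilutes a true heart-failure effect, so it serves as a check on the heart-failure result and cannot replace it.
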